#### Sample

The goal for Aim 2 is to recruit 24 adults; 12 individuals in the mobile and technology-assisted aftercare group and 12 individuals in the standard services group. These adults will be recruited equally across the three participating jurisdictions resulting in eight participants per county. Individuals brought to the CSU by law enforcement will be randomly assigned to one of two study conditions in equal proportions. To be eligible for participation in Aim 2, individuals must be age 18 or older, English speaking, will discharge to one of three participating counties and plan to remain in the county for 6 months, admitted to the CSU through law enforcement, consent, and the cognitive capacity to understand study participation and to consent. This sample size is strategically small due to testing the feasibility of accessing the needed sample size for future studies. With this pilot sample size, we will be looking at the feasibility of recruiting individuals in a vulnerable, highly transient, population, and retention trends. Both feasibility of recruitment and retention trends will impact our decision on a larger sample size in the subsequent RCT.

#### Recruitment

Research participants for Aim 2 will be recruited into the study at our partner mental health agency’s CSU prior to their discharge. CSU patients will be flagged as potential research participants by an agency staff member. This staff member flags CSU patients based on whether a patient meets the inclusion criteria. Once the research team is alerted of the potential participants, the research team will go on-site to ensure eligibility. Eligible CSU clients will be informed of the research study and provided details of participation by the research team member. Informed consent will be obtained after performing a cognitive assessment. The cognitive ability to consent will be determined through the brief capacity to consent screener, a tool that checks comprehension of participating in the study—cognitive capacity is re-assessed at subsequent data collection points when warranted. Potential participants will be given the option to consent to participate by the research team member at this time.

#### Randomization

In Aim 2, participants who will be recruited from the CSU will be randomized into either the control group (treatment as usual) or the intervention group (technology-assisted mobile aftercare) by the research team. Due to the short length of stay in a CSU, the research team will use a one-to-one randomization procedure and pre-randomize the pool of participants prior to recruitment. To do so, the research team will create an allocation table with the total participant slots (*n*=24) and then use a random sequence generator to pre-randomize each slot as either the control group or the intervention group. The randomized allocation table will be uploaded into our online database where the randomization status will only be visible to the research team member upon completing the consent process with a participant. Following these guidelines eliminates the potential for human error or bias into who receives the mobile aftercare intervention. Participants will be notified of their randomization status at the end of the consent and baseline data collection interview by the research team. It is necessary to inform the participants of their randomization group because the interventionist will contact participants in the treatment group within 24 hours to set up their first appointment.

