#### Analysis strategy

Data collected from the Mobile and Technology-Assisted Aftercare and Standard Services Groups will allow researchers to gather preliminary data comparing those that receive standard CSU services to those that receive CSU services plus the mobile and technology-assisted aftercare support. Patterns will be monitored to assess the primary and secondary outcomes listed in Table 3. A mixed-data analysis plan, including descriptive statistics (means, proportions, frequencies, and percentages) and bivariate analyses, will be used to capture the range of qualitative and quantitative data present in this study’s primary and secondary outcomes. The study is not designed to detect differences in clinical outcomes; thus, the focus of the analysis provides preliminary information on trends in outcomes and some potential underlying contributors to those trends. These data will provide essential information for advancing knowledge of CSUs and information necessary to inform the future RCT. Qualitative data related to the primary outcomes will be analyzed using the approach described in the Aim 1 analysis strategy. Quantitative analysis for primary outcomes will be conducted using a comparative analysis both within groups and across time. The bivariate analysis will be used to assess correlations and regressions. Additionally, preliminary ANOVAs will be used to assess the trends of participants. Qualitative and quantitative data will be combined using a sequential mixed methods design. Equal weight will be given to the qualitative and quantitative data sources. Data will be reviewed and analyzed for any significant variations that can help assess trends in participants over time and across groups through mean comparison tests.

Mixed methods analysis will be used to assess both primary and secondary outcomes. We will integrate the findings from each of the quantitative and qualitative components [56] by conducting comparative analyses both within and across groups, over time, so that we may examine differences at the county level in terms of quality and fidelity of the intervention. Data will be integrated with quantitative outcome measures, fidelity data, and qualitative interviews using a sequential mixed methods design with equal weight given to qualitative and quantitative data sources [56, 57]. Data will be assessed for significant variations, and qualitative data is used to help us understand quantitative data trends when warranted.

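### The single 24-slot allocation table, as described, has no link to county, although enrolment is set at eight per county and a county-level look at fidelity and quality is planned

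*Protocol article*

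**What the plan says.** All references are to the protocol article, Aim 2.

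- **Sample.** "The goal for Aim 2 is to recruit 24 adults", split as "12 individuals in the mobile and technology-assisted aftercare group and 12 individuals in the standard services group". The section continues: "These adults will be recruited equally across the three participating jurisdictions resulting in eight participants per county". Participants are to be "randomly assigned to one of two study conditions in equal proportions". Eligibility requires discharge to one of three participating counties, so county is known before allocation.
- **Randomization.** "the research team will use a one-to-one randomization procedure and pre-randomize the pool of participants prior to recruitment". The team will "create an allocation table with the total participant slots" (24 of them) and then "use a random sequence generator to pre-randomize each slot as either the control group or the intervention group". The table sits in the online database, and the assignment is shown to the team member only after consent is complete. No county list, stratum or block is mentioned, and no rule states that the table is constrained to 12 and 12.
- **Analysis strategy.** Comparisons within and across groups over time are planned in order to "examine differences at the county level in terms of quality and fidelity of the intervention".

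**The concern.** The Sample section fixes two margins, 12 per arm and eight per county. The procedure in the Randomization section secures at most the first of them, and leaves the split of arms inside each county to chance.

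Two things are at stake. First, fidelity is monitored only in the intervention arm, and feasibility is measured by sessions completed per participant. What can be learnt about delivery in a county therefore depends on how many people there were allocated to the intervention. Second, arm comparisons are descriptive, but the first progression criterion asks whether the results suggest positive effects in the treatment group. A chance association between arm and county could colour that reading with 12 per arm.

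**Working it through.** **Inputs.** 24 participants, 12 per arm, three counties, eight per county (Sample); one table of 24 slots (Randomization). Assumptions: all 24 are enrolled, exactly eight per county, and the order in which counties enrol is unrelated to the order of the list.

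**The plan's own figures.** 3 × 8 = 24 and 12 + 12 = 24, so the two margins agree. There is no power-based sample size to reproduce.

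**Reading A: one list constrained to 12:12, county ignored.** There are C(24,12) = 2,704,156 equally likely lists. The number with a, b and c treated in the three counties is C(8,a)·C(8,b)·C(8,c), with a + b + c = 12.

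- All three counties 4:4: 70³ / 2,704,156 = 343,000 / 2,704,156 = 12.7%. At least one county is off 4:4 in 87.3%.
- A given county 4:4: 70 × 12,870 / 2,704,156 = 33.3%.
- A given county with one or none treated: C(8,0)·C(16,12) + C(8,1)·C(16,11) = 1,820 + 34,944 = 36,764 lists. Two counties cannot both be in this position, because the third would need at least ten treated. So for any county: 3 × 36,764 / 2,704,156 = 4.1%.
- A given county with two or fewer treated: 36,764 + C(8,2)·C(16,10) = 36,764 + 224,224 = 260,988 lists. Two counties can both be at two only if the third is at eight, which gives 3 × 28 × 28 = 2,352 lists. So for any county: (3 × 260,988 − 2,352) / 2,704,156 = 780,612 / 2,704,156 = 28.9%.

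**Reading B: each slot generated independently at 1:1.**

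- Exactly 12:12 overall: 2,704,156 / 2²⁴ = 16.1%. A split of 15:9 or worse occurs in 30.7%.
- All three counties 4:4: (70/256)³ = 2.0%.
- Some county with two or fewer treated: P(X ≤ 2) = 37/256 = 14.5% for one county, so 1 − (1 − 37/256)³ = 37.4%.

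**With three county lists of eight, each fixed at 4:4.** Every county is 4:4 and the trial is 12:12 with certainty, provided each county fills its eight slots.

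**Predictability.** In a list with m slots per arm, the expected number of final slots that follow with certainty from the earlier ones is 2m/(m + 1).

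- One 12:12 list: 24/13 = 1.8.
- Three 4:4 lists: 3 × 8/5 = 4.8.

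**The case against.** - **County is inferred from silence.** The Randomization section is compressed, the 24 slots might already be laid out by county, and a fuller protocol might specify strata. This is possible. But the article states the mechanism as one table with each slot pre-randomised, and nothing in it points to county strata.
- **The slot-by-slot reading strains the text.** The 12 and 12 target and the one-to-one wording favour a constrained list, for which overall imbalance is zero. This stands. The 16.1% shows what an ambiguous sentence permits, not the expected outcome.
- **The county analysis is modest.** It concerns quality and fidelity, not treatment effects by county, and is descriptive. Fidelity is sampled by session, one a week, with up to 26 sessions per participant. Even perfect balance gives only four treated per county. Under Reading A every county has at least two treated in 100% − 4.1% = 95.9% of lists. This stands and limits the weight of the point. A county with many treated yields more fidelity data, so the count of counties at 2:6 or worse in either direction (38.6% under Reading A) overstates the loss; the 28.9% is the relevant figure.
- **This is a pilot.** Secondary outcomes are not meant to measure impact, and with 12 per arm chance imbalance on many factors cannot be avoided. This is fair. County is nevertheless the one factor that the plan both fixes by quota and intends to examine.
- **Stratifying has a price.** More final slots become predictable, and if a county under-fills, three separate lists no longer guarantee 12:12. Both points are correct and belong in the decision.

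**Conclusion.** The point holds as a cheap improvement to a stated procedure. As described, the table does not secure the within-county balance that eight per county and equal allocation would permit. Under the likelier 12:12 list, all three counties are balanced in 12.7% of lists, and some county has two or fewer treated in 28.9%. The practical cost is thin intervention data in a county, and possibly some mixing of arm with county in the descriptive comparisons.

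A reader might infer two stronger things. One is that the arms will be unequal overall. The document does not support this as the expected result, since its target and its one-to-one wording favour a constrained list; overall imbalance arises only if slots are generated independently. The other is that county differences will confound the arm trends. The article refers to variation between jurisdictions only in general terms and gives no figure for it. Recruitment, the support specialists and standard follow-up all run through the one partner agency. The size of any confounding is therefore unknown.

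The percentages rest on full enrolment of eight per county and on county order being unrelated to list order.

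**What to change.** Replace the single table with three county lists of eight slots, each constrained to four intervention and four control. Select the list in the existing database by discharge county, and keep each assignment concealed until consent is complete, as already planned. State in the Randomization section that the lists are constrained and not generated slot by slot.

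This needs no extra participants and no new system. The costs are those shown above:

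- About 4.8 instead of 1.8 final slots become predictable to someone who knows the list structure and the past allocations, so the block structure should not be disclosed to recruiters.
- Overall 12:12 is assured only if each county fills its eight slots.

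Varying the block sizes and having the lists generated by someone who does not recruit are optional additions; the core change does not depend on them.

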#### Intervention description

The mobile and technology-assisted intervention is designed as an aftercare program for persons released from a CSU and addresses treatment retention barriers by combining in-person assistance and technology-aided tools. The aftercare program will be delivered to participants by Community Support Specialists (CSSs) who are employees of our partnering behavioral health agency and trained in the research study protocol. The aftercare program will be delivered up to once a week for 6 months or 26 sessions; the needs of each participant determine the frequency of sessions.

The mobile and technology-assisted aftercare program services will include the CSSs providing in-person assistance by meeting with participants at their homes or nearby public settings and providing participants with 24/7 access to behavioral health services through mobile applications. During sessions, the CSSs will provide various assistance, including social support, psychoeducation on behavioral health, and health management skills, and assist with the navigation of community resources, including housing, meeting basic needs, and other tangible supports that promote community stability. To provide support in-between session work, the CSSs will give guidance on using the mobile apps that are relevant to the participant. Additionally, CSSs will employ motivational interviewing and solution-focused brief therapy techniques in the sessions. The mobility of the aftercare program differs from standard services in which persons are expected to return to the behavioral health agency approximately 1 month after discharge from the CSU. The mobile and technology-assisted aftercare program is based on the Community Health Model (CHW) wherein mobile CHW solutions provide resources, counseling, education, and assistance to vulnerable and disadvantaged populations [29, 30]. Similar to CHW programs, a vital component of the CSS work is augmenting interventions at our partner mental health agency by providing community-based services and mobile app support to address client barriers to treatment directly.

The technology-assisted component of the mobile and technology-assisted aftercare program includes 24/7 access to behavioral health mobile applications. These apps are free for the participants and uploaded onto their own smartphones. If the participant does not have a reliable access to a smartphone or does not wish to have the apps uploaded to their phone, they will be provided a smartphone for free by the research team. Participants who are provided a smartphone will have the phone bill covered by the research team for the duration of their participation in the research study. Upon completion or termination of the study, the research team will cease paying the phone bill, but participants may keep the phone. The mobile applications serve to augment the in-person support provided by the CSS. The CSS will recommend one or more mobile applications from a menu of evidence-based applications based on the participant’s diagnosis and treatment goals. The intervention strictly differs from standard services in this aspect because standard services do not connect individuals to mental and behavioral health mobile applications.

Mobile applications incorporated into this intervention include Moodtools-Depression Aid, Virtual Hope Box, Recovery Path, and Intellicare Hub. All mobile-based applications have undergone thorough investigation in one or a combination of RCTs/clinical trials, were developed with mental health professionals, and have shown a positive impact on intended outcomes [31–36]. Participants will not be required to use the mobile applications. However, the participants will be encouraged to use the apps by the CSS. The CSS will incorporate dialogue and instruction on the utilization of the apps into the intervention sessions. Specifically, during sessions, the CSS will ask participants about their use of the apps, what they like and do not like, and provide information on how the app(s) may assist the participant in reaching their goals. The CSS will not record, track, or obtain any data from the mobile apps on the participant’s phones. If participants do not wish to use the apps, they will not have to. The research team will not track, record, or obtain any data from the apps on the participant’s phones. The research team will collect data on the use of the apps through an open-ended question measure, Qualitative Technology Use, described in “Measures” section. The above mobile applications were chosen for a variety of reasons, including their development standards, accessibility for download, and range of mental health and substance use-related tools and resources that are promising and apply to our intervention and population.

Standard care for persons discharging the CSU will include a personalized discharge plan and a follow-up appointment with the agency within a month for evaluation and continued mental health services. At the follow-up appointment, participants may be connected to other agency services. These services include outpatient counseling for behavioral and emotional problems, psychiatric services, group therapy, case management, rehabilitation services, homeless recovery services, employment services, medication-assisted treatment, group-based team-building activities, a primary care clinic, and forensic services. Individuals may also receive referrals for applicable healthcare services, access to residential and outpatient substance abuse treatment services, and access to a tablet.

#### Fidelity monitoring

Fidelity monitoring is a set of practices that help researchers measure how well an intervention is delivered and the extent to which it is delivered as intended. We will conduct fidelity monitoring to ensure participants receive the mobile and technology-assisted aftercare as it is designed and be confident that the CSSs have the necessary skills and knowledge to implement the services. Fidelity monitoring will be conducted with participants engaged with the mobile and technology-assisted aftercare intervention study condition. We adapted the fidelity monitoring tool used for this study from the Well-Being Development Program Fidelity Tool used in a multi-site randomized controlled trial of a behavioral health intervention designed for justice-involved individuals [37]. This adapted tool includes a measure that assesses motivational interviewing with the participants for sessions where this therapeutic technique is used. The research project manager will complete the on-site observation of the intervention. Due to the mobile nature of the intervention, the CSS will meet with the participants in various settings. The project manager will randomly select one session to monitor each week. After the session, the project manager will review the fidelity monitoring ratings with the CSS to give feedback. A CSS who scores lower on the fidelity ratings will receive additional training in the intervention to improve the likelihood that they can improve and maintain fidelity.

#### Measures

Measures for the Mobile and Technology-Assisted Aftercare Group and Standard Services Group include administrative records and direct data collection from participants. The primary outcomes for this feasibility study are participant recruitment, participant retention, feasibility, and the acceptability of the intervention. Participant recruitment will be measured by the number of eligible participants who consent to participate out of the total number of eligible participants. Participant retention will be measured by the proportion of the intervention completed by participants. Feasibility and accessibility will be assessed by triangulating the qualitative and quantitative data from study participants—the CSU professionals and patients.

 The secondary outcomes include individual stabilization and well-being, frequency of both acute and long-term treatment use, re-admission to a crisis stabilization unit, and arrest rates or re-encounters with law enforcement. The secondary outcomes will be assessed to find trends that will inform the future RCT. We will examine the feasibility of collecting the data, the sensitivity of the measures, estimates for effect size and sample size, and other factors that may impact the ability to detect outcomes. For the pilot study, the secondary outcomes are not meant to measure impact; instead, they are intended to examine trends in outcomes to inform the design of the intervention and study protocol for the future RCT. Secondary outcomes will be measured using screening questions, demographical information, clinical assessment tools, and baseline and follow-up interviews with each participant. Administrative data from the CSUs and law enforcement will be collected on client characteristics, including demographics (e.g., race, gender, age, county of residence), criminal history (e.g., current reason for law enforcement contact, prior arrests, and reasons for arrest, and prior CSU stays), and behavioral health status (e.g., diagnoses, prior and current treatment utilization, and medication-assisted treatment). Table 3 shows the measures related to each secondary outcome described below.

**Table 3 Tab3:** Primary and secondary measures

**Primary outcomes**	**Measures**
Participant retention	Number of recruited participants who complete the intervention
Participant recruitment	Number of eligible participants who agree to participate out of the total number of eligible participants
Feasibility of intervention	Number of intervention sessions completed by each participant
Acceptability of intervention	Qualitative interviews with CSU stakeholders
**Secondary outcomes**	**Measures**
Individual stabilization and well-being	Brief Symptom Inventory Brief COPE Hearth Hope Index Trauma History Questionnaire Financial security Education and employment Education employment aspiration and satisfaction Network composition survey
Acute and long-term treatment use	Service assessment for children/adults California Psychotherapy Alliance Scale Qualitative CSU experience Qualitative technology use
Admission into CSU	Administrative data of re-admission into CSU
Arrest rates/re-encounters with law enforcement	Administrative data of arrest rates Lawbreaking Police-community interaction survey

The Brief Symptom Inventory [38] is a 53-item assessment covering nine dimensions through subscales: somatization, obsession-compulsion, interpersonal sensitivity, depression, anxiety, hostility, phobic anxiety, paranoid ideation, and psychoticism. Scores for each subscale range from 0 to 4, with higher scores meaning more symptoms reported. Reported internal consistency reliability ranged from *⍺*=0.75 to 0.89 [39], test-retest reliabilities ranged from 0.68 to 0.91, acceptable convergent validity, and construct validity [40].

The Brief COPE [41] assessment is a 28-item index that assesses coping self-efficacy and confidence coping with stress using an intensity scale of 1 to 4. The higher the score, the greater the coping self-efficacy. The Brief COPE has been found to have acceptable reliability *⍺*=0.81 [42].

The Herth Hope Index [43] is a 12-item measurement tool that assesses hope, self-efficacy, and the respondent’s outlook on life. The tool uses an intensity scale from 1 to 4, where the higher reported scores indicate a higher level of hope. The Herth Hope Index has been used in 10 countries and has shown acceptable reliability and acceptability across 13 studies [44].

The 25-item Trauma History Questionnaire (THQ) assesses the occurrence of specific traumatic experiences, including interpersonal violence, accidents and disasters, serious illness, traumatic loss, and criminal victimization. Participants will indicate if they have experienced the event with dichotomous “yes” or “no” questions. Respondents are then asked to self-report the age they were at the time of the incident and the frequency of the trauma. The THQ operationalizes the Diagnostic and Statistical Manual of Mental Disorders, 5th edition (DSM-5) criteria for trauma exposures. The THQ has been found to be a reliable measure of trauma exposure (3-month test-retest coefficients=.51–.91) and has strong convergent validity to other measures (*k*=.61–1.00) [45].

The eight-item financial security measure was conceptually created from the work of Mills et al. [46] and adapted for an RCT trial of a behavioral health-focused intervention for justice-involved individuals [47]. The measure assesses an individual’s ability to pay for one’s bills, basic needs, and potential unexpected expenses without difficulty. Various intensity scales (0 = none/never to 5 = all of the time) are included alongside dichotomous “yes” and “no” questions—the lower the score, the more financial stability.

The Education and Employment assessment is an 11-item questionnaire that measures past and current employment, sources of income, and education level. The Education Employment Aspiration and Satisfaction [48] survey is a 13-item assessment that measures an individual’s satisfaction with their current employment and education levels. The assessment uses an intensity scale of 1 to 4 for both the education and employment subscales. Higher scores for the education subscale indicate higher satisfaction and aspiration to obtain additional education. Higher scores on the employment scale indicate higher satisfaction and aspirations to improve their work situation. The scale has been shown to have acceptable reliability (*⍺*=0.79 to 0.90) across the four subscales and sufficient criterion-related validity [48].

